## Abstract

Prostate cancer (PCa) is the most common malignancy in men worldwide. Multiparametric MRI (mpMRI) improves the detection of clinically significant PCa (csPCa); however, it remains limited by false-positive findings and inter-observer variability. Time-dependent diffusion (TDD) MRI provides microstructural information that may enhance csPCa characterization beyond standard mpMRI. This prospective observational diagnostic accuracy study protocol describes the evaluation of PROS-TD-AI, an in-house developed AI workflow integrating TDD-derived metrics for zone-aware csPCa risk prediction. PROS-TD-AI will be compared with PI-RADS v2.1 in routine clinical imaging using MRI-targeted prostate biopsy as the reference standard.

## 1. Introduction

### 1.1. Prostate Cancer Epidemiology

Prostate cancer (PCa) is a major global health challenge. The 2022–2027 National Cancer Plan’s official communication, based on GLOBOCAN data, reported that lung, prostate, and colorectal cancers are the three most common malignancies among men worldwide [1]. PCa is the most frequently diagnosed cancer in men in 118 of 185 countries. Cancer incidence varies according to socioeconomic development. Countries undergoing economic transition face an increased risk of certain cancers, particularly breast cancer in women and PCa in men. In Latin America, the overall cancer mortality rate is projected to increase by more than 100% in the coming years [1].

### 1.2. Overall Prostate Cancer Diagnostic Workflow

Risk-adaptive algorithms first combine prostate-specific antigen (PSA), digital rectal exam (DRE), prior biopsy, family history, and routine pre-biopsy multiparametric MRI (mpMRI). mpMRI classifies lesions with a Prostate Imaging–Reporting and Data System (PI-RADS) score from 1 to 5 to estimate the likelihood of clinically significant prostate cancer (csPCa). If the MRI is negative (PI-RADS 1–2) and clinical suspicion is low (e.g., PSA density < 0.20 ng/mL/cc; for PI-RADS 3, <0.10), biopsy will be deferred with PSA follow-up; otherwise, targeted and perilesional biopsy should be performed for higher scores (PI-RADS ≥ 4), in accordance with EAU–EANM–ESTRO–ESUR–ISUP–SIOG guidelines [2]. Prostate cancer aggressiveness is graded using the Gleason score (GS) or International Society of Urological Pathology (ISUP) grade groups. A score of ≥7 GS or ISUP ≥ 2 indicates highly cellular, clinically significant disease, which is more likely to progress and therefore requires active treatment [3].

### 1.3. Relevance of Non-Invasive Evaluation by mpMRI

Multiparametric MRI has reshaped prostate cancer care by detecting clinically significant disease while reducing unnecessary biopsies and overtreatment of clinically insignificant lesions [4,5,6]. Standard mpMRI combines T2-weighted (T2W), contrast-enhanced, and diffusion-weighted imaging, which are scored on the PI-RADS scale to estimate csPCa likelihood and guide biopsy decisions [7,8]. The updated PI-RADS v2.1 further improved tumor detection within the transition zone by 7–18 percentage points [9].

### 1.4. Diagnostic Limitations and Inter-Observer Variability in mpMRI

Despite these advances, mpMRI remains vulnerable to both false-negative and false-positive results. The inter-observer agreement for PI-RADS is moderate to substantial, with reported κ values of 0.62–0.70 for v2.0 and 0.70–0.72 for v2.1 [10,11]. Moreover, diagnostic accuracy varies widely across studies applying PI-RADS v2.1, with a reported sensitivity of 72–96.3%, specificity 62–93.5%, positive predictive value 53–78%, and negative predictive value 64–94.3% [12,13,14,15]. This variability hampers reliable interpretation for clinical decision-making. Further development of MRI techniques is needed to improve diagnostic performance, enabling accurate differentiation between benign diseases, non-clinically significant prostate cancer (non-csPCa), and csPCa, thereby reducing unnecessary biopsies and supporting cost-effective, imaging-based risk prediction.

### 1.5. Time-Dependent Diffusion MRI

Time-dependent diffusion (TDD) MRI is a relatively new sequence that probes water molecule diffusivity over short diffusion times, potentially revealing the tissue microstructure beyond single-cell resolution. Early animal studies demonstrated sensitivity to microscopic tumor features [16,17,18,19]; however, clinical adoption was limited by the need for very high gradient strengths [20,21].

Recent pilot studies on head and neck, breast, and prostate cancers demonstrated technical feasibility even with limited diffusion time ranges [22,23,24,25]. Using high-performance gradients (≤80 mT/m), Xu et al. advanced biophysical modeling to extract quantitative microstructural maps from TDD data; however, this approach was not yet feasible for routine diagnostics [23,26]. A breakthrough was achieved when Wu et al. showed that standard clinical MRI systems could acquire TDD images that distinguished csPCa from non-csPCa, exploiting the stronger diffusion-time dependence observed in highly cellular, high-grade tumors [27]. This line of research advances the concept of virtual prostate pathology using non-invasive imaging methods.

### 1.6. Further Possibilities with the TDD Sequence

Further validation of TDD microstructural parameters for PCa imaging must follow a staged evidence framework that confirms the following: (1) technical adequacy for better lesion detection; (2) diagnostic accuracy; (3) influence on physicians’ clinical reasoning; and (4) impact on patient management, culminating in outcome assessment within Fryback and Thornbury’s hierarchical model [28,29]. Independent real-world studies should avoid biases, such as the enriched prostatectomy sample used by Wu et al. [27], which may overestimate test performance. Finally, TDD invites the development of quantitative MRI metrics, moving beyond simple parameter averaging, to provide objective, low-variability tissue characterization that can inform clinical guidelines.

### 1.7. Deep Learning-Based Interpretation

Accurate lesion localization is essential because the peripheral and transition zones of the prostate differ markedly in architecture and cancer prevalence [30]. Advances in deep learning (DL) have enabled automated zone segmentation on both mpMRI and transrectal ultrasound, making zone-specific assessment feasible in routine practice [31,32].

Therefore, future work should evaluate zone-specific diagnostic performance of TDD-derived microstructural parameters and test machine learning algorithms for imaging-based PCa risk estimation, particularly given that reproducibility remains hampered by high inter-observer variability [33]. Within the standard diagnostic workflow, novel imaging techniques aim to reduce unnecessary biopsies by offering accurate and non-invasive detection of csPCa [34].

Accordingly, this study will prospectively assess the diagnostic contribution of TDD-derived imaging metrics integrated into an AI-based interpretation framework by comparing their performance in predicting csPCa against PI-RADS v2.1-driven mpMRI in real-world clinical practice. In line with this, the primary objective is to evaluate whether the AI-enhanced TDD-MRI pipeline (PROS-TD-AI) improves the classification of clinically significant prostate cancer (csPCa; ISUP grade group ≥ 2) within the PI-RADS 3–4 decision zone compared with standard PI-RADS v2.1 (with the primary endpoint being the paired specificity improvement for csPCa classification). The secondary objectives are as follows: (1) to develop and evaluate an automated prostate segmentation model (reporting the Dice similarity coefficient); (2) estimate TDD microstructural parameters and perform lesion/tissue classification (reporting AUC, accuracy, sensitivity, and specificity with 95% CIs); and (3) assess the integrated end-to-end PROS-TD-AI pipeline combining imaging and clinical features, including robustness and failure modes.

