## 2. Materials and Methods

### 2.1. Study Design

This is a prospective, observational, and analytical study, incorporating an exploratory component aimed at developing and validating a novel MRI protocol and an AI-based interpretation framework named PROS-TD-AI DL for prostate zonal segmentation and lesion classification. This study will be conducted at the Clinical Hospital of the University of Chile (HCUCH) and the Faculty of Medicine of the University of Chile. This protocol follows a paired (within-subject) diagnostic–accuracy comparison, as each participant contributes both the standard PI-RADS assessment and PROS-TD-AI output, with biopsy used as the reference standard when performed. The protocol is approved by the Institutional Review Board (or Ethics Committee) of the University of Chile Clinical Hospital (protocol code 1339/23, approved on 9 May 2023). No commercial entity participated in the design of this study, nor will any be involved in its execution or analysis. Reporting will follow the STARD-AI guideline for diagnostic accuracy studies involving artificial intelligence; a completed STARD-AI checklist with page/section references is provided in Supplementary Table S1 [35].

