#### 2.5.4. Model Governance

Versioning: All AI components (segmentation, parameter estimation, and classification) will be version-controlled (code, pre-processing, and trained weights). The final selected model will be locked (frozen parameters) prior to final evaluation, and any subsequent modifications will be released as a new version and evaluated separately.Bias Mitigation: To mitigate bias and leakage, data splitting is performed at the patient level only, with stratification by csPCa status; all pre-processing, feature selection, calibration, and threshold tuning will occur within training folds. We will report performance stratified by clinically relevant subgroups (e.g., peripheral vs. transition zone; PI-RADS category) to assess heterogeneity.Explainability: The system will output clinician-facing results, including ROI overlays and lesion-level probability scores. For model transparency, we will report feature importance/attribution (e.g., permutation importance or SHAP for tree-based models) and calibration summaries, while emphasizing that explainability outputs are supportive and not used for ground-truth determination.Monitoring: We will prospectively log non-evaluable cases and failure modes (e.g., missing sequences, motion/artifacts, and segmentation/fit failure) and report their frequency and impact on performance. During this observational study, PROS-TD-AI outputs will not influence clinical management.

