The primary endpoint is the paired improvement in specificity (non-csPCa correctly recommended as “3”) of PROS-TD-AI-assisted recommendations versus standard PI-RADS (4 vs. 3), tested using McNemar’s test [49], in the non-csPCa subgroup (two-sided alpha = 0.01). The secondary endpoints include paired sensitivity in csPCa (McNemar), upgrade/downgrade reclassification rates stratified by pathology, and continuous-score discrimination (ROC AUC) and calibration (*p* < 0.05 for secondary analyses). We will present 2 × 2 cross-tabulations (index test vs. reference standard) for PI-RADS and PROS-TD-AI recommendations in the biopsy-verified PI-RADS 3–4 cohort, including counts of TP, FP, TN, and FN. Baseline demographic, clinical, and technical characteristics will be summarized for each analysis split (training/validation/test and the prospective evaluation cohort) to assess representativeness and potential distribution shift, including age, PSA/PSA density, prostate volume, PI-RADS category, and key acquisition variables (scanner/vendor and sequence quality markers). Because participants are consecutively enrolled within the routine intended-use pathway (biopsy-verified PI-RADS 3–4), we expect the csPCa prevalence to reflect this clinical setting. We will report the observed csPCa prevalence and discuss any material deviation as potential spectrum effects affecting generalizability.

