### 3.2. Pipeline Integration

We propose an end-to-end deep learning pipeline that combines anatomical segmentation with microstructure-based tissue classification. The pipeline will be trained end-to-end using a deep neural network that combines imaging data with clinical features, thereby simultaneously optimizing segmentation and classification objectives. This joint learning approach enables shared feature representation, enhancing both anatomical delineation and microstructural characterization. By integrating diffusion-informed biomarkers with anatomical information, this framework is expected to improve diagnostic accuracy and provide clinically meaningful predictions.

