## 4. Discussion

This protocol is designed to prospectively develop and evaluate novel imaging techniques and analytic approaches aimed at improving non-invasive detection of csPCa. By integrating time-dependent diffusion MRI (TDD-MRI) with AI-based quantitative analysis, this study seeks to enhance diagnostic specificity, reduce the reliance on invasive biopsy procedures, and provide accurate, low-risk, and more accessible risk stratification for men at intermediate clinical risk.

Demonstrating higher specificity and reliable performance of these novel imaging methods could have a significant impact on both research and clinical practice. Positive findings would provide a foundation for future randomized controlled trials and support evidence-based updates to current standard-of-care diagnostic workflows, potentially leading to more personalized and efficient patient management.

PROS-TD-AI may offer its greater incremental clinical value in diagnostic scenarios where mpMRI interpretation is most equivocal and PI-RADS exhibits lower specificity, particularly for PI-RADS 3–4 [51] lesions and transition-zone/central gland abnormalities, in which benign prostatic hyperplasia and stromal changes can closely mimic clinically significant disease [9]. In these settings, the addition of TDD-derived microstructural biomarkers and quantitative AI-based analysis may improve discrimination and reduce inter-reader variability, thereby refining risk stratification around biopsy decision thresholds and potentially decreasing unnecessary biopsies without compromising sensitivity for csPCa diagnosis.

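### The only test-versus-test comparison is the whole PROS-TD-AI pipeline against PI-RADS, so the added value of TDD itself is not estimated

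*Protocol article*

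**What the plan says.** Section 1.7 states the general aim: "this study will prospectively assess the diagnostic contribution of TDD-derived imaging metrics integrated into an AI-based interpretation framework". The same sentence continues "by comparing their performance in predicting csPCa against PI-RADS v2.1-driven mpMRI in real-world clinical practice". The primary objective that follows is worded for the AI-enhanced TDD pipeline against PI-RADS v2.1. Secondary objective 2 reports how well TDD parameters classify lesions or tissue. Secondary objective 3 is to "assess the integrated end-to-end PROS-TD-AI pipeline combining imaging and clinical features, including robustness and failure modes".

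Section 2.1 describes the pairing: "each participant contributes both the standard PI-RADS assessment and PROS-TD-AI output". In section 2.9 the primary endpoint is the paired specificity gain "of PROS-TD-AI-assisted recommendations versus standard PI-RADS (4 vs. 3), tested using McNemar’s test", in men without csPCa. Paired sensitivity and the reclassification rates concern the same two assessments, and section 2.10 sizes the study on them.

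Section 2.9 compares four classifiers. It selects for specificity subject to a sensitivity floor and sets the cutoffs by that criterion. Section 3.2 describes training the pipeline "using a deep neural network that combines imaging data with clinical features". For transparency, section 2.5.4 promises "feature importance/attribution (e.g., permutation importance or SHAP for tree-based models", and calls explainability outputs supportive.

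**The concern.** The index test differs from its comparator in more than one respect. It adds TDD metrics, a trained classifier and cutoffs tuned for specificity; PI-RADS is a fixed 4-versus-3 cut. In the integrated pipeline it also adds clinical features. No planned comparison removes TDD and keeps the rest.

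A significant McNemar result would thus look the same whether TDD supplied most of the gain or little of it. The study could meet its primary endpoint and still not say whether the extra 4.5-minute sequence adds diagnostic information beyond what standard mpMRI and a tuned classifier provide. Section 4 expects that "the addition of TDD-derived microstructural biomarkers and quantitative AI-based analysis may improve discrimination". That joint statement is one the design can address only jointly.

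**Working it through.** **1. The plan's own figure.** Section 2.10 gives two-sided alpha 0.01, 80% power, p10 = 0.15 and p01 = 0.05, hence a difference of 0.10 and total discordance of 0.20.

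n = (2.576 + 0.842)² × 0.20 / 0.10² = 11.683 × 20 = 233.7, rounded up to 234. Then 234 / 0.62 = 377.4, or 378 in total; 378 / 0.90 = 420 and 378 / 0.85 = 445.

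The arithmetic reproduces. All of it sizes the pipeline against PI-RADS.

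**2. What each planned analysis can say about TDD.**

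| Planned analysis | Section | What it estimates | Gain over the same approach without TDD? |
|---|---|---|---|
| Paired specificity and sensitivity, reclassification | 2.9 | Whole pipeline against PI-RADS | No |
| AUC and calibration of the score | 2.9 | Performance of the pipeline score | No |
| Four candidate classifiers | 2.9 | Choice of algorithm; no comparison by inclusion of TDD is stated | No |
| TDD classification accuracy | 1.7 (objective 2), 2.6 | TDD performance with no comparator | No |
| ANOVA or Kruskal–Wallis across tissue groups | 2.9 | Association with grade | No |
| Permutation importance or SHAP | 2.5.4 | Use of inputs by one fitted model | No, because nothing is refitted without TDD |

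**3. Which inputs the classifier uses.** Sections 2.5.3, 2.6 and 2.9 describe TDD-derived metrics. Clinical features appear only in secondary objective 3 (section 1.7) and in section 3.2. Section 2.9 does not list the classifier inputs. If only TDD metrics enter, the trained classifier and tuned cutoffs are still bundled with them. If clinical features also enter, the bundle is larger. The attribution problem exists either way.

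**4. What a with-TDD versus no-TDD contrast could show.** The inputs are 234 men without csPCa in the evaluation cohort (section 2.10) and two-sided 0.05, the level section 2.9 gives for secondary analyses. The total discordance D between the two models is an assumption, because the document gives none.

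Difference detectable with 80% power = (1.960 + 0.842) × √(D / 234):
- D = 0.10: 2.802 × 0.02067 = 0.058
- D = 0.15: 2.802 × 0.02532 = 0.071
- D = 0.20: 2.802 × 0.02924 = 0.082

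For an assumed TDD increment of 0.05, power = Φ[(√234 × 0.05 − 1.960 × √D) / √(D − 0.05²)]:
- D = 0.10: Φ[(0.765 − 0.620) / 0.312] = Φ(0.46), about 68%
- D = 0.20: Φ[(0.765 − 0.877) / 0.444] = Φ(−0.25), about 40%

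The 95% CI half-width at that increment, 1.960 × √[(D − 0.05²) / 234], is 0.040 at D = 0.10 and 0.057 at D = 0.20.

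**The case against.** The strongest reply is that aim and endpoint agree. The sentence on diagnostic contribution names PI-RADS as its comparator and describes the TDD metrics as part of an AI framework; the primary objective is worded for the pipeline; and the endpoint and sample size follow from it. This stands. A reader might infer that the primary comparison is invalid. The document does not support that: it is a valid test of the pipeline.

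A reader might also infer that a positive result could come entirely from clinical features. The document does not establish this, since the methods sections describe TDD metrics as the training data and never say that clinical variables enter the locked recommendation.

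Nor is TDD otherwise unexamined. Its standalone accuracy is reported, and permutation importance does measure loss of performance when an input is scrambled. It does so within one fitted model, though, and correlated inputs can distort it; it is not the performance of a model built without TDD.

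Two further objections carry some weight. The detectable differences are 58% to 82% of the whole planned 0.10 gain, so a test on this contrast would be well powered only if TDD drove most of it. That argues for estimation, not for leaving the contrast out. An ablation might also sit in a fuller plan that is not shown. But this article itself states the aim, the comparator and the endpoints, and the contribution of TDD cannot be read from the comparison they define.

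**Conclusion.** The point holds in limited form. The primary analysis answers whether PROS-TD-AI as a whole has better specificity than PI-RADS 4 versus 3. It does not answer the broader aim of section 1.7 about what TDD contributes, and no other planned analysis fills that gap. The share of the planned 0.10 gain due to TDD cannot be quantified from the document.

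The planned data could support a useful estimate, with 80% power at two-sided 0.05 for differences of roughly 0.06 to 0.08. This rests on all 234 men being in the evaluation cohort and on assumed discordance of 0.10 to 0.20. An increment of 0.05 would be detected with only about 40% to 68% power. This is an improvement the sponsor should make, not a defect in the primary test.

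**What to change.** Add a secondary, estimation-focused analysis:

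- State the inputs of the main classifier.
- Train a no-TDD model on conventional mpMRI features, plus clinical features if the main model uses them. Use the same folds, candidate classifiers, selection rule and sensitivity floor.
- Make the contrast nested: the main model should include the same non-TDD inputs, or a version of it that does should be reported alongside.
- Lock the no-TDD model at the same time as the main model and apply it unchanged to the same evaluation cohort.
- Report paired differences in specificity, sensitivity and AUC with 95% CIs, and attribute benefit to TDD only on this contrast.

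If the sponsor declines, the aim in section 1.7 and the study's conclusions should be limited to the pipeline as a whole.

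The cost is one more model (and a nested version, if needed) and one more analysis, on data already to be collected; no extra patients, scans, readers or biopsies are needed. The drawbacks are limited power for small increments, and the chance that the TDD-specific gain proves smaller than the headline gain over PI-RADS.

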## 2. Materials and Methods

### 2.1. Study Design

This is a prospective, observational, and analytical study, incorporating an exploratory component aimed at developing and validating a novel MRI protocol and an AI-based interpretation framework named PROS-TD-AI DL for prostate zonal segmentation and lesion classification. This study will be conducted at the Clinical Hospital of the University of Chile (HCUCH) and the Faculty of Medicine of the University of Chile. This protocol follows a paired (within-subject) diagnostic–accuracy comparison, as each participant contributes both the standard PI-RADS assessment and PROS-TD-AI output, with biopsy used as the reference standard when performed. The protocol is approved by the Institutional Review Board (or Ethics Committee) of the University of Chile Clinical Hospital (protocol code 1339/23, approved on 9 May 2023). No commercial entity participated in the design of this study, nor will any be involved in its execution or analysis. Reporting will follow the STARD-AI guideline for diagnostic accuracy studies involving artificial intelligence; a completed STARD-AI checklist with page/section references is provided in Supplementary Table S1 [35].

